### Statistics

***Description of statistical methods*.** The primary statistical analysis will be by intention-to-treat (ITT). Between group comparisons will be presented using effect measures (ratio or difference in response rate, difference in means) with 95% confidence intervals.

The primary outcome will be modelled using a generalised linear mixed effect logistic model, adjusting for flu season (first or second season), age, sex, GP practice and chronic illnesses. The outcome will be presence of any of the listed symptoms (feverishness, cough, sore throat, malaise, headache, myalgia, shortness of breath and temperature) rated as moderate or severe by participants who meet the protocol ILI definition on any of the days that are included for study purposes. Random effects will be incorporated to account for the clustering of participants within households and to account for the clustering of data over days within participant.

Comparison between groups of the proportion of participants experiencing an ILI will be carried out using the same method as the. The mixed effects will acknowledge the clustering of participants within households. The effect measure presented for MVA-NP+M1 compared to IIV alone will be an adjusted odds ratio with 95% confidence interval, which can be interpreted as an adjusted relative risk given the low prevalence.

We will use mixed-effect model, or an equivalent nonparametric method where appropriate, to analyse continuous secondary outcomes, adjusting for the same baseline measures and stratification variables. We will compare the safety outcomes using Chi-squared or Fisher’s exact test.

All the tests will be done at a 5% two-sided significance level. Data analysis will be restricted to the periods where acute respiratory illnesses are likely to be attributable to influenza based on local and national surveillance intelligence.

***Immunogenicity analyses*.** In the immunology sub-cohort, the primary analysis will be to assess the difference in magnitude of influenza-specific T-cell (using interferon gamma enzyme-linked immunospot assay) and antibody responses (using influenza hemagglutination inhibition assay) between the two groups. We will assess the vaccine immunogenicity by comparing the change in these immunological parameters from baseline to 21 days after vaccination between the groups, and how this varies according to baseline factors of age, gender and chronic illness. To assess the durability of immune responses post-vaccination, the stability of immunological parameters between the post vaccine time point and end of season time point will be assessed. The immunological x will be log transformed (based 10) and we will use appropriate regression or correlation methods to carry out the analysis.

***Reporting procedures for adverse events*.** All adverse events (AEs) occurring in the first 28 days post-vaccination are captured in the diaries. The relationship of each AE to the trial medication is determined by a medically qualified individual. All AEs that result in a patient’s withdrawal from the study will be followed up until a satisfactory resolution occurs, or a non-study related causality is assigned. All reported severe symptoms are reviewed by the Medical Monitor in the first 4 weeks.

***Reporting procedures for SAEs*.** All SAEs are documented and reported according to the Pharmacovigilance SOP. The assessment of expectedness is made by a clinician using the reference safety information current at the time of the event. If deemed necessary un-blinding will occur in accordance with trial specific working instructions.

***Group holding rules*.** If a group holding rule is activated, further vaccinations won’t occur until it is deemed appropriate to restart, by the MHRA: if more than 30% of vaccinations are followed by the same Grade 3, solicited local AE or solicited systemic AE or unsolicited AE, beginning within 2 days after vaccination and persisting at Grade 3 for >48 hrs. Other events that trigger the rule include related death, life-threatening reaction, SUSAR, acute allergic reaction or anaphylactic shock. The study can also be put on hold upon advice of the Chief Investigator, Sponsor, MHRA, REC or DMEC.

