### Randomisation

The study team obtain the randomised group allocation through a validated and secured web-based server (Sortition®). Randomisation will use non-deterministic minimisation on practice, age and gender to ensure each arm is balanced and 1:1 allocation when all participants have been recruited. The immunology sub-cohort will be randomised separately using the same method. Emergency randomisation procedure is also available if the web-based system isn’t accessible.

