### Sample size

We assumed the average number of days spent with moderate or severe ILI per “season” of circulation was 3.5 days and a typical follow-up period for a season of approximately 120 days across this corresponds to 2.92% of days [6]. A sample size of 2,030 (1,015 per group) will provide 85% power to detect a relative drop of 20% in the primary outcome between the two groups (from 2.92% to 2.34%) at 5% level of significance (2-sided). This sample size has accounted for a 25% attrition rate and a further 15% increase to account for clustering of participants within households, which are estimated to be 0.04.

For the secondary outcomes, we estimated that 12.25% of vaccinated individuals over 65 years old experience an ILI most likely attributable to influenza [6].The proposed sample size will have 90% power to a reduction in the percentage of individuals experiencing ILI from 28.5–22.25%. We estimate a 50% improvement in vaccine efficacy over the IIV alone in reducing the occurrence of ILI due to influenza during periods of influenza circulation.

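### The odds ratio for ILI is to be read as a relative risk because ILI is rare, yet the trial is powered on 28.5% of controls having one

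*Protocol article*

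**What the plan says.** Two sections of the protocol article bear on this point.

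- **Statistics, Description of statistical methods.** The paragraph on the proportion of participants who have an ILI specifies a mixed model with household clustering. The effect measure is an "adjusted odds ratio with 95% confidence interval, which can be interpreted as an adjusted relative risk given the low prevalence".
- **Sample size.** For the secondary outcomes, the trial is said to have "90% power to a reduction in the percentage of individuals experiencing ILI from 28.5–22.25" (per cent).

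Table 3 (Objectives) lists incidence of ILI as the first secondary outcome. The primary outcome, days with moderate or severe ILI, has its own rate in the Sample size section: 2.92% of days, falling to 2.34%.

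**The concern.** An odds ratio approximates a risk ratio only when the outcome is uncommon in both arms. The article justifies the approximation by low prevalence, but its own planning figure says that more than one control participant in four will have an ILI. The premise and the planning figure cannot both be right.

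For any real effect on a common outcome, the odds ratio lies further from 1 than the risk ratio. If the vaccine works, reading one as the other makes it look better than it is. The error is systematic, so a larger sample does not reduce it. The Sample size section frames the expected effect on influenza-attributable ILI as a relative improvement in vaccine efficacy, so a relative reduction is the figure readers will look for and that later trials may be planned on.

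There is a smaller, related issue. The planned odds ratio is conditional on a household random effect and on covariates. That moves it a little further from the population risk ratio.

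**Working it through.** **Inputs**

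| Quantity | Value | Source |
|---|---|---|
| ILI proportion, control (p1) | 28.5% | Sample size |
| ILI proportion, MVA-NP+M1 (p2) | 22.25% | Sample size |
| Participants per arm | 1,015 | Sample size |
| Stated power | 90% | Sample size |
| Significance level | 5%, two-sided | Statistics |
| Household clustering figure | 0.04 | Sample size |

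**Step 1: reproduce the stated power.** This shows whether 28.5% and 22.25% are the working participant-level proportions.

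- Pooled proportion: (0.285 + 0.2225)/2 = 0.25375.
- Standard error under the null: √(2 × 0.25375 × 0.74625/1015) = 0.01932.
- Standard error under the alternative: √[(0.285 × 0.715 + 0.2225 × 0.7775)/1015] = 0.01927.
- Power: Φ[(0.0625 − 1.96 × 0.01932)/0.01927] = Φ(1.28) = 0.8995.

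This matches the stated 90%, so these are the proportions of participants with an ILI on which the comparison was planned. The match uses all 1,015 per arm, with no allowance for attrition or clustering. That is a separate matter and does not affect what follows.

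**Step 2: risk ratio and odds ratio at the planned proportions.**

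- RR = 0.2225/0.285 = 0.781, a relative reduction of 21.9%.
- OR = (0.2225/0.7775)/(0.285/0.715) = 0.2862/0.3986 = 0.718. Read as a relative risk, this is a reduction of 28.2%.
- Overstatement: 28.2 − 21.9 = 6.3 percentage points. In relative terms, 28.21/21.93 − 1 = 29%.
- Risk difference: 28.5 − 22.25 = 6.25 percentage points.

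In general OR = RR × (1 − p1)/(1 − p2). Here the multiplier is 0.715/0.7775 = 0.920. It would have to be close to 1 for the stated reading to be safe.

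**Step 3: is there any rate in the article for which the reading is safe?**

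| Outcome | p1 → p2 | RR | OR | Reduction from RR | Reduction from OR |
|---|---|---|---|---|---|
| Participants with an ILI | 28.5% → 22.25% | 0.781 | 0.718 | 21.9% | 28.2% |
| Influenza-attributable ILI, halved | 12.25% → 6.125% | 0.500 | 0.467 | 50.0% | 53.3% |
| Days with moderate or severe ILI (primary) | 2.92% → 2.34% | 0.801 | 0.797 | 19.9% | 20.3% |

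The approximation is good only for the per-day primary outcome. If the treated-arm ILI proportion is instead taken as 28.5% less half of 12.25%, that is 22.375%, the RR is 0.785 and the OR 0.723. The conclusion is the same.

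**Step 4: effect of the household random intercept.** Assume that the 0.04 is an intraclass correlation on the latent logistic scale. The random-intercept standard deviation is then √[(0.04/0.96) × π²/3] = 0.370. Solving for the conditional odds ratio that gives marginal proportions of 28.5% and 22.25% yields 0.712, against 0.718 marginally. For assumed correlations from 0.01 to 0.30, the conditional odds ratio runs from 0.717 to 0.664. At the article's own figure the extra shift is small.

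**The case against.** The strongest case on the other side has five parts.

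- **The damage is limited.** ILI incidence is a secondary outcome. No test, p-value, allocation or data collection changes, and a labelled odds ratio with its interval is a valid estimate. All of this stands.
- **The reading is optional.** The article says that the odds ratio can be interpreted as a relative risk. It does not say that one minus the odds ratio will be reported as efficacy. That is literally true, but the relative reduction follows directly once the ratio is read as a relative risk, and the article endorses that reading on a premise it contradicts.
- **Other measures are already allowed.** The opening of the Statistics section permits ratios or differences in response rate. This helps, but it is a general line, and the later sentence names the odds ratio for this outcome and says how to read it.
- **The clause may belong to the primary outcome.** The sentence introducing the ILI comparison is cut short where it refers to a shared method, and low prevalence does fit 2.92% of days. If so, the justification is attached to the wrong outcome and still needs correcting.
- **The difference is modest against sampling error, and it works both ways.** With all 1,015 per arm and no clustering, the 95% interval for a risk ratio of 0.781 is about 0.67 to 0.91. An apparent harm would be exaggerated just as a benefit would. Both are correct, but the shift is a known bias and not chance, and it favours the vaccine in the scenario that the trial is designed to detect.

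The random-effect argument adds little at 0.04, and the conclusion does not depend on it.

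**Conclusion.** The concern holds. The low-prevalence premise is contradicted by the proportions on which the same outcome is powered. At those proportions, the stated reading turns a 21.9% relative reduction into 28.2%, an overstatement of 6.3 percentage points or about 29% of the effect. The size rests on the planned 28.5% and 22.25%. If ILI proves much rarer than planned the gap shrinks, but the plan cannot rely on that. The point affects the interpretation of the first-listed secondary efficacy outcome only.

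**What to change.** Delete the clause that lets the odds ratio be read as a relative risk. For the proportion with an ILI, report an adjusted risk ratio and an adjusted risk difference with 95% intervals, using the covariates already planned. Two routes are available:

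- Keep the logistic mixed model and standardise it, averaging predicted risks under each allocation over the covariates and the household effect.
- Fit a modified Poisson (log-link) model with household-cluster-robust standard errors for the risk ratio, and obtain the risk difference by standardising its predictions.

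The odds ratio can remain as a supportive estimate, labelled as such. Deleting the clause alone would remove the contradiction. Adding the risk ratio and risk difference also gives readers the quantity they would otherwise try to extract from the odds ratio.

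The cost is a change of wording and a few lines of code, with no new data. The reported effect will look smaller: at the planned figures, about 22% instead of 28%. The choice should be fixed before results are known, so that it cannot appear to follow from them.

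### Safety outcomes get unadjusted tests although allocation is minimised on practice, age and gender: still valid, but slightly conservative for common events if those factors predict them

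*Protocol article*

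**What the plan says.** All references are to the protocol article.

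- **Randomisation:** "Randomisation will use non-deterministic minimisation on practice, age and gender to ensure each arm is balanced and 1:1 allocation".
- **Statistics, primary outcome:** a mixed-effect logistic model, "adjusting for flu season (first or second season), age, sex, GP practice and chronic illnesses", with random effects for household and for days within participant.
- **Statistics, ILI incidence:** the sentence naming the method breaks off, but the stated effect measure is an adjusted odds ratio.
- **Statistics, continuous secondary outcomes:** a mixed-effect model or a nonparametric equivalent, "to analyse continuous secondary outcomes, adjusting for the same baseline measures and stratification variables".
- **Statistics, safety:** "We will compare the safety outcomes using Chi-squared or Fisher’s exact test". No covariates are named.
- **Statistics, significance level:** "All the tests will be done at a 5% two-sided significance level". Between-group comparisons are to be given as effect measures with 95% confidence intervals.

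Table 3 lists safety and reactogenicity among the secondary objectives, with solicited reactions, unsolicited adverse events and serious adverse events as outcomes 6 to 8.

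**The concern.** Minimisation makes the arms more alike on practice, age and gender than simple randomisation would. If these factors predict an outcome, the between-arm difference in proportions varies less from trial to trial than a plain two-sample test assumes. The assumed standard error is then too large, the true size falls below 5%, and some power is lost.

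In an efficacy comparison, a conservative test guards against a false claim. In a harm comparison, it makes a true excess in the MVA-NP+M1 arm a little harder to show. The plan applies adjustment to its efficacy outcomes and departs from it for safety without giving a reason. The covariates are already planned for the efficacy models, so adjusting costs little.

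**Working it through.** **1. The plan's own figure.** The protocol states no power and no expected rate for any safety comparison. Its only anchor is the primary outcome: "A sample size of 2,030 (1,015 per group) will provide 85% power to detect a relative drop of 20% in the primary outcome". Comparing 2.92% with 2.34% of days (two-sided 5%, 85% power, pooled variance under the null) needs 13,668 person-days per arm. If 0.04 is read as the correlation between days within a participant, although the text attaches it to households, the design effect is 1 + 119 × 0.04 = 5.76. Then 13,668 × 5.76 / 120 = 656 per arm; / 0.75 = 875; × 1.15 = 1,006; total 2,012. That is 0.9% below 2,030. The trial size is therefore taken as given: 2,030 randomised, and about 2,030 × 0.75 = 1,522 after the planned attrition.

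**2. Analytic size of the effect.** Let R² be the share of outcome variance explained by the balanced factors. With arms balanced on them, the unadjusted z statistic has standard deviation √(1 − R²) instead of 1. Starting from 80% power for the adjusted test:

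- size = 2[1 − Φ(1.96/√(1 − R²))]
- power = Φ(2.80 − 1.96/√(1 − R²)), where 2.80 = 1.96 + 0.84
- the interval is too wide by the factor 1/√(1 − R²)

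| R² | true size | power (adjusted 80%) | interval too wide by |
|---|---|---|---|
| 1% | 4.9% | 79.7% | 0.5% |
| 5% | 4.4% | 78.5% | 2.6% |
| 10% | 3.9% | 76.9% | 5.4% |
| 15% | 3.4% | 75.0% | 8.5% |

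**3. Simulation.** Biased-coin minimisation on practice, age band and sex; chi-squared compared with logistic regression on the same three factors. Assumptions not in the protocol: 20 practices, three age bands, coin probability 0.8, event rate about 30%, OR 1.38 for treatment, 1,522 analysed, 2,000 runs per cell. Monte Carlo standard error is about 0.5 points for size and 0.8 to 1.0 for power.

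| Prognostic strength (assumed) | size, chi-squared / adjusted | power, chi-squared / adjusted |
|---|---|---|
| weak: sex OR 1.3, age OR 0.9 per band, practice SD 0.2 | 4.6% / 4.9% | 82.8% / 83.5% |
| moderate: sex OR 2, age OR 0.75, SD 0.3 | 4.5% / 5.1% | 82.3% / 84.1% |
| strong: sex OR 3, age OR 0.6, SD 0.6 | 3.4% / 5.3% | 73.2% / 77.9% |

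The gains are 0.7, 1.8 and 4.7 points. A second simulation used all 2,030 participants, 4,000 runs, an event rate of about 20–30% and a treatment log-OR of 0.28. With R² about 3% it gave 79.7% against 80.8%; with R² about 9% it gave 75.2% against 78.8%.

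**4. Why rare events do not matter here.** To first order, R² ≈ p(1 − p)s², where p is the event rate and s² the variance of the factors on the log-odds scale. For the moderate scenario, s² = (ln 2)²/4 + (2/3)(ln 0.75)² + 0.3² = 0.120 + 0.055 + 0.090 = 0.265. At p = 30%, R² ≈ 0.21 × 0.265 = 5.6%. At p = 1%, R² ≈ 0.0099 × 0.265 = 0.26%, and the formula in step 2 then gives 79.9% instead of 80%.

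For rare events the choice between the two unadjusted tests matters far more. By exact enumeration at 1,015 per arm:

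| Event rates | chi-squared power | Fisher power |
|---|---|---|
| 0.5% vs 1.5% | 64.4% | 55.0% |
| 1% vs 2.5% | 75.0% | 68.9% |
| 3% vs 5.5% | 80.5% | 77.3% |

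That loss comes from the discreteness of Fisher's test, not from minimisation.

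**The case against.** The strongest reply is that nothing here is wrong. Chi-squared and Fisher tests stay valid after minimisation, unadjusted comparison of many binary adverse event outcomes is common practice, and supportive adjusted analyses can be left to an analysis plan. Validity and common practice stand, which is why this is an improvement and not an error. But the article does fix the method for safety, so the choice is open to comment.

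The power comparison is also not size-matched, because the adjusted test rejected slightly more than 5% under the null. In the 2,030-participant simulation its size was 5.2% and 5.4%. Bringing it to a true 5% by a normal approximation lowers 80.8% to about 80.3% and 78.8% to about 77.8%, so the gains fall from 1.1 and 3.6 points to about 0.6 and 2.6. The excess is itself within Monte Carlo error, so this is indicative only. It does mean that the simulated gains are, if anything, on the high side.

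Three stronger readings are tempting, and the document supports none of them:

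- **That the harm comparison is conservative outright.** This depends on practice, age and gender predicting adverse events, on which the protocol gives no information. If they do not, there is no loss.
- **That safety alone departs from an otherwise uniform adjusted analysis.** The immunogenicity section leaves its regression or correlation methods open, and continuous outcomes may be analysed nonparametrically.
- **That the trial could miss a safety signal for this reason.** Group holding rules, Medical Monitor review of severe symptoms, committee review of possibly related serious events and three interim safety reviews do not rest on this test.

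**Conclusion.** The point holds in a conditional and modest form. The planned safety tests ignore factors on which allocation is balanced and for which the efficacy models adjust. They keep type I error at or below 5% in this respect, but they give up some precision to the extent that those factors predict adverse events. For common outcomes such as any solicited reaction, the cost is about 1 to 2 power points with weak to moderate factors and 4 to 5 only with strong ones. For rare outcomes such as serious adverse events it is immaterial. Every figure rests on assumed event rates, number of practices and prognostic strength. It is a low-priority improvement, worth making because it is nearly free.

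**What to change.** Replace the safety sentence with wording to this effect:

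*Common binary safety outcomes (any solicited local reaction, any solicited systemic reaction, any unsolicited adverse event) will be compared between arms with a logistic model adjusted for age, sex, season and chronic illness, with practice and household as random effects. The adjusted odds ratio, or a risk difference obtained by standardisation, will be reported with its 95% CI. Outcomes with fewer events than a threshold fixed before unblinding, including serious adverse events and individual rare events, will be compared with the unadjusted test. The same test is the fallback if the model does not converge.*

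A logistic model does not yield a risk difference directly. Standardisation means averaging each participant's predicted risk under both arms and taking the difference. The result is easier to set beside the crude event tables than a conditional odds ratio.

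The covariates match the planned efficacy model. The gains shown above come from adjusting for practice, age and sex alone, with practice as a fixed effect; nothing is claimed for the other terms, which are there for consistency.

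Cost: slightly more programming, an event-count threshold that must be stated in advance, and some risk of non-convergence with many practices, which the fallback covers. No additional participants are needed.

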To assess the safety and reactogenicity of MVA-NP+M1 in combination with licensed inactivated influenza vaccine in adults ≥65 years. To assess the immunogenicity of MVA-NP+M1 or Placebo in combination with the recommended licensed inactivated influenza vaccine in adults aged 65 years and above To assess the presence of the influenza virus using virological markers, in adults aged 65 years and above vaccinated with MVA- NP+M1 or Placebo in combination with the recommended annual licensed inactivated vaccine	6. Occurrence of solicited local and systemic reactogenicity signs and symptoms for 7 days following vaccination 7. Occurrence of unsolicited adverse events for 28 days following vaccination 8. Occurrence of serious adverse events throughout participants’ participation in the trial - Frequency of influenza-specific T-cells measured by IFN-γ ELISpot - Geometric mean titre of influenza-specific neutralising antibodies - Breadth of influenza-specific T-cells and antibodies 1. Incidence rate of laboratory confirmed influenza using RT-PCR.	Day 0–7 - Self-reported symptoms recorded using electronic or paper diaries Day 0–28 - Self-reported symptoms recorded using electronic or paper diaries Telephone calls on Day 1–3, day 7–9 and every 3–4 weeks throughout participants’ participation in the trial Blood samples drawn at enrolment (before vaccinations), day 21 and at the end of the influenza season Nasal swab sample taken by participant at the time of self-reported symptoms. Nasal swabs will be taken during the first 3 days of the onset of the self-reported symptoms
**Tertiary Objectives** To explore novel clinical endpoints for future Phase III efficacy trials of influenza vaccines	1. Estimated frequency of influenza infection using historical data on the proportion of ILIs that is caused by influenza virus infection.	At the end of the influenza season

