### Study design

The trial is an individually randomised, participant-blinded, placebo-controlled, multi-centre phase IIb efficacy study in 2030 volunteers aged 65 and over, in England. The main study is set in primary care and a separate immunology sub-cohort of 100 participants will be recruited at the Jenner Institute, University of Oxford. The trial will be promoted through various media sources.

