### Sub-cohort

A sub-cohort of participants (50 for each of two seasons) will be recruited to assess the immunogenicity of MVA-NP+M1 in combination with the licensed IIV. In addition to the procedures described for the main cohort, the sub-cohort attend a screening visit, and three further visits where blood samples are taken for monitoring of laboratory AEs and immunology purposes at weeks 1, 3 and 26. Blood samples will be stored in compliance with the Human Tissue Act (2004).

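### The immunogenicity comparison is set on change from baseline without naming the measured baseline value as a covariate; naming it would gain precision at no cost

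*Protocol article*

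**What the plan says.** The immunogenicity paragraph of the Statistics section fixes the measure: T-cell (ELISpot) and antibody (haemagglutination inhibition) responses are assessed by "comparing the change in these immunological parameters from baseline to 21 days after vaccination between the groups". The same paragraph asks "how this varies according to baseline factors of age, gender and chronic illness". It then says that values are log10 transformed and leaves the model to suitable regression or correlation techniques.

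Earlier in that section, continuous secondary outcomes are to be adjusted for the same baseline measures as the primary model. Those are flu season, age, sex, GP practice and chronic illness. Neither list includes the participant's own baseline ELISpot or antibody value.

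That value will exist. Table 3 (Objectives) has "Blood samples drawn at enrolment (before vaccinations), day 21 and at the end of the influenza season".

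On size, Study design says "a separate immunology sub-cohort of 100 participants will be recruited", and the Sub-cohort section says "A sub-cohort of participants (50 for each of two seasons) will be recruited". On allocation, Randomisation says "The immunology sub-cohort will be randomised separately using the same method", which is minimisation on practice, age and gender with "1:1 allocation when all participants have been recruited".

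**The concern.** A plain between-group comparison of change subtracts the whole baseline value from each day-21 value, so it treats the slope of day 21 on baseline as exactly 1. If the true slope is below 1, subtraction over-corrects: the change remains negatively correlated with baseline, and baseline noise enters the treatment contrast. Letting the data estimate the slope removes that noise.

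This matters because the sub-cohort is small, about 50 per arm, and is the only source of T-cell and antibody data that the article describes. Minimisation does not include baseline immunity, so some chance imbalance between arms on that variable must be expected. The data needed to deal with it are already being collected. As the text stands, an unadjusted comparison of change would comply with the plan.

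**Working it through.** **Inputs from the article.** Sub-cohort 50 × 2 seasons = 100, which agrees with the total in Study design. Allocation is 1:1, so about 50 per arm. Tests are two-sided at 5%. The article gives no power, SD, effect size or baseline-to-day-21 correlation for the immunogenicity comparison, so there is no stated power figure to reproduce.

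**Assumed.** rho, the within-arm correlation of log10 baseline with log10 day 21, is taken over a range. The SD s is first taken as equal at both times.

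**Variances.** Per participant, up to the common factor 2/50 for the difference between arms:

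- unadjusted change: 2(1 − rho)s²
- baseline-adjusted: (1 − rho²)s²
- ratio adjusted/unadjusted: (1 − rho)(1 + rho) / [2(1 − rho)] = (1 + rho)/2

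The reduction in confidence interval width is 1 − √[(1 + rho)/2]. The number needed with unadjusted change to match 100 with adjustment is 100 / [(1 + rho)/2].

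| rho (assumed) | Variance ratio | CI width narrower by | Unadjusted N matching 100 adjusted | Power, unadjusted change | Power, adjusted |
|---|---|---|---|---|---|
| 0.3 | 0.65 | 19% | 154 | 56% | 75% |
| 0.5 | 0.75 | 13% | 133 | 70% | 82% |
| 0.7 | 0.85 | 8% | 118 | 90% | 94% |
| 0.9 | 0.95 | 2.5% | 105 | about 100% | about 100% |

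Power is for an illustrative true difference of 0.5 SD with 50 per arm. If the 25% attrition assumed for the main trial also applied here, the pairs at rho 0.3, 0.5 and 0.7 would be 45% and 62%, 58% and 70%, and 80% and 86%. Below rho 0.5, unadjusted change is also less precise than comparing day-21 values alone, because 2(1 − rho) then exceeds 1.

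**Where the lost precision goes.** The gap between the two variances is 2(1 − rho) − (1 − rho²) = (1 − rho)². With equal SDs the slope is rho, so a baseline difference d between arms moves the unadjusted change estimate by −(1 − rho)d. The standard error of d is √(2/50) = 0.2 SD. At rho 0.5, an imbalance of one standard error therefore moves the estimate by 0.5 × 0.2 = 0.1 SD. Its sign is random, so over repeated randomisations this is variance, not bias.

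**Unequal SDs.** If the day-21 SD is k times the baseline SD, the ratio is k²(1 − rho²) / (1 + k² − 2·rho·k). Over rho 0.3 to 0.9 this runs from 0.41 to 0.49 at k = 0.7, and from 0.81 to 0.99 at k = 1.3. The gain may thus be large or negligible.

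**Simulation check.** With 4,000 simulated sub-cohorts of 50 per arm at rho 0.5 and a true difference of 0.5 SD, the mean estimate was 0.495 for both methods, so neither is biased. The empirical standard errors were 0.198 (unadjusted) and 0.172 (adjusted), a variance ratio of 0.758 against 0.75 from the formula. Regressing change on arm plus baseline gave the same treatment estimate as regressing the day-21 value on arm plus baseline, as the algebra requires: moving the baseline to the left-hand side only lowers its coefficient by 1.

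**The case against.** The strongest reply is that the article says what is compared and leaves open how. Change from baseline can be the outcome of a regression that includes the baseline value, and the result is then identical to an analysis of covariance on day 21. The covariate list for a sub-cohort analysis commonly sits in the statistical analysis plan or full protocol, neither of which is shown. If the general rule for continuous secondary outcomes covers immunogenicity, season, age and sex are already planned.

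Much of this stands. A reader might infer that the sponsor has decided against baseline adjustment. The article does not say so, and its open wording on methods is compatible with adjustment. A reader might also infer that chance imbalance biases the comparison. It does not: under randomisation the change comparison is unbiased on average, and imbalance costs precision. The size is uncertain too. It rests on an assumed rho and on equal SDs, it is slight at high rho, and there is no stated immunogenicity power for it to undermine.

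What the reply does not remove is that the article goes beyond silence. It fixes change as the measure and names the baseline factors of interest, and the one likely to be the most informative is absent from both of its lists. Permission to adjust does not secure adjustment.

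**Conclusion.** The point holds as an improvement in efficiency, not as an error that threatens validity. The article commits to a comparison of change in about 50 participants per arm and does not commit to using the measured baseline as a covariate. If the analysis were run unadjusted, it would give up 35%, 25%, 15% or 5% of the variance at rho 0.3, 0.5, 0.7 or 0.9, assuming equal SDs at the two times. With a day-21 SD 0.7 or 1.3 times the baseline SD, the loss over the same range of rho would run from 51% to 59% or from 1% to 19%. The article supplies neither rho nor the SDs, so no single figure should be quoted as the loss. If the analysis plan already includes the baseline value, nothing is lost and the article only needs the clarification.

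**What to change.** Add one sentence to the immunogenicity paragraph: the log10 day-21 response (or, equivalently, the log10 change) will be regressed on arm with the log10 baseline value of the same assay as a covariate, alongside the covariates already planned, and the treatment effect will be reported as an adjusted geometric mean ratio with its 95% confidence interval.

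Keep the durability analysis from day 21 to the end of the season as stated, because it asks whether responses are stable. A baseline-adjusted comparison of the end-of-season values answers a different question; it may be added but should not replace it.

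The cost is that sentence and one degree of freedom per model. No new samples, visits or assays are needed.
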